#### Recruitment: cancer services and staff

An initial meeting (face to face or via teleconference) will be held, attended by representatives of the ADAPT research team, the Head of the cancer service, and representatives of the psychosocial, nursing, clinical trial and IT staff. At this meeting, the study will be described in detail, and potential interest in participation will be ascertained. Interested cancer services will be asked to identify a local ADAPT champion, and to sign an ADAPT Research Participation Agreement.

All staff employed on a permanent or ongoing (6 months or more) basis, either full or part time or as a visiting medical officer, in a role that provides clinical care to patients with cancer or client focussed administrative support or IT/managerial support, will be invited to participate in the study. Staff will be identified as part of the organisation chart mapping exercise during site engagement. Site champions will identify and approach eligible staff, to whom they will explain the study. Interested staff will be contacted by the research team and provided with a written information sheet and consent form to sign.

A site, or individual cancer service staff member, may withdraw from the study and elect to have their data removed from the study database. If a site chooses to withdraw prior to completion of baseline data collection, and there is sufficient time within the study timeline, the site will be replaced by a reserve list site pre-randomised to the same study arm.

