Awareness campaign	• Roadshow presentation by ADAPT staff at the site 8 weeks before “go-live” • Poster displayed prominently 4 weeks prior to and at “go-live,” (T0) • Email from site champion to all staff 1 week before “go-live” (T0)	• Additional posters at 4-monthly intervals during implementation • Newsletters emailed to site staff at 2, 4, 6, 9 and 12 months
Champions	• Champion identification and role definition • Provision of email templates for champion to send staff • Inclusion of champion contact details in all staff communication	• Additional proactive contact with Champions at monthly intervals to discuss progress, provide audit reports and discuss additional implementation strategies as needed
Academic detailing and support	• Sites provide with a written report summarising change readiness data from baseline staff interviews at T0 • Tailoring of the ADAPT Portal to site requirements during engagement meetings • Study close meeting with all key staff to discuss sustainability of the ADAPT CP	• Sites provided with a verbal report of these data, at T0, T1 and T2 • Quarterly review of ADAPT Portal configuration to confirm allocated responsibilities and service tailoring
Reporting	• Monthly written reports on Portal statistics	• Presentation and highlighting of issues from monthly reports in face-to-face meetings with site
Technological support	• IT support for the ADAPT Portal	

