### Study procedures and timeline

Randomisation will be performed by the study statistician using online randomisation software (STATA). Allocation concealment will be preserved; both sites and ADAPT Program staff conducting assessments will remain blinded until study completion. Following randomisation, sites will undertake a 3-month period of engagement to clarify study procedures, train staff in the ADAPT CP and use of the ADAPT resources, and tailor the ADAPT Portal to local site resources and preferences. Study sites will then complete baseline (T0) staff questionnaires and interviews to ascertain staff views on service and staff readiness to adopt the ADAPT CP. The online questionnaires will be available on RedCap (Research Electronic Data Capture) [29] and automatically downloaded to a database to reduce possible bias. The ADAPT research team will follow-up those participants who do not complete or return their questionnaire within 2 weeks, with up to three reminder emails or phone calls at different times of the day. A subset of staff with key roles in implementing the ADAPT CP will be invited to participate in an audio-recorded semi-structured interview exploring their views of the ADAPT CP, barriers and facilitators to its use and site readiness.

Sites will then “go-live,” integrating the ADAPT CP into clinical care for a 12-month implementation period. Staff will be encouraged to introduce the ADAPT CP to all patients as part of routine care, and on their verbal consent, register them into the ADAPT Portal. Patients will then be asked to access the ADAPT Portal for efficient screening and data collection, information and access to ADAPT resources. Staff will be asked to respond to ADAPT emails and alerts for patients who require further assessment and referral. ADAPT research staff will administer Core versus Enhanced implementation strategies as per randomisation during this period.

Mid-way through the 12-month implementation period (T1 at 6 months) and at the end of the implementation period (T2 at 12 months), questionnaire data will again be collected from cancer service staff, and a subset of cancer service staff will participate in an audio-recorded semi-structured interview to ascertain staff views on implementation outcomes, and awareness of and perceived utility of the ADAPT CP implementation strategies.

Timing of enrolment, engagement, intervention and data collection is shown in Table 2.

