**Table 2 Tab2:** Schedule of enrolment, engagement, intervention and data collection

		Study period					
	Enrolment	Engagement	Allocation	Intervention			Costs retrieval
Timepoint	-T2	-T1	0	T0 “Go-live”	T1 6 mths	T2 12 mths	T3 3 mths post
Enrolment:							
Eligibility Screen	X						
Informed Consent	X						
Governance	X						
Engagement:							
Role definition		X					
Tailoring		X					
Staff training		X					
Allocation			X				
Interventions:							
Core				X	X	X	
Enhanced				X	X	X	
Assessments:							
Primary outcome							
Adherence: CP					X	X	
Secondary outcomes							
Acceptability				X	X	X	
Adoption					X	X	
Appropriateness				X	X	X	
Feasibility				X	X	X	
Costs				X	X	X	X
Penetration					X	X	
Sustainability						X	
ORIC, Hands4U, study-developed organisational readiness items				X	X	X	
Demographic & disease items				X			

Case report forms (CRFs) in this study will take the form of site profile forms, contact logs, implementation strategy checklist and observational diaries, implementation strategy data psycho-social activity data and Medicare Data forms completed by ADAPT Program staff to collect service level data and staff surveys completed by cancer service staff participants. All other quantitative data will be collected electronically via the ADAPT portal. Additionally, the research team will conduct internal audits by reviewing automated reports built into the ADAPT Portal to ensure system functioning, correctness and accuracy of data entry.

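### Text and Table 2 disagree on whether sites are randomised before or after engagement, neither says the arm stays undisclosed until staff consent and T0 are complete, and the claim that sites remain blinded cannot hold as written

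*Protocol article*

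**What the plan says.** All references are to the Protocol article.

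- **Sequence in the text.** Under Study procedures and timeline: "Following randomisation, sites will undertake a 3-month period of engagement to clarify study procedures, train staff in the ADAPT CP". Portal tailoring belongs to the same period. The baseline follows: "Study sites will then complete baseline (T0) staff questionnaires and interviews to ascertain staff views on service and staff readiness". Go-live comes after that.
- **Sequence in the table.** Table 2, titled "Schedule of enrolment, engagement, intervention and data collection", orders its columns Enrolment, Engagement, Allocation, then T0 with go-live. Role definition, tailoring and staff training are marked under Engagement, before Allocation.
- **Staff recruitment.** Under Recruitment: cancer services and staff: "Staff will be identified as part of the organisation chart mapping exercise during site engagement". Site champions then approach eligible staff, and consent follows.
- **Replacement.** The same section says that if a site leaves before its baseline data are complete, and time allows, "the site will be replaced by a reserve list site pre-randomised to the same study arm".
- **Blinding.** Study procedures and timeline states that allocation is concealed and that "both sites and ADAPT Program staff conducting assessments will remain blinded until study completion".
- **Difference between arms.** Interventions/groups describes a passive approach for Core, with extra help only on request, and an active one for Enhanced. Table 1 gives Enhanced sites, for example, "Additional proactive contact with Champions at monthly intervals to discuss progress".

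**The concern.** In a cluster trial, whatever happens between allocation and the start of the intervention is protected only if the people involved do not know the arm. Three things may fall in that window here.

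1. Champions choose which staff to approach. If they know the arm, the staff samples may differ between arms.
2. Staff give their T0 views on readiness and attitudes. Secondary hypothesis 12 compares the arms on improvement from T0 to 6 and 12 months. If T0 answers are influenced by knowing the arm, the measured change is distorted, in a direction that cannot be predicted.
3. Sites may withdraw and be replaced. If leaving, or accepting a reserve place, depends on a known arm, the set of sites analysed is no longer purely the product of randomisation.

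The blinding statement matters separately. A reader who takes it at face value would judge the risk of bias in the staff-reported outcomes to be lower than it is.

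**Working it through.** No arithmetic decides this point. The check is to set the sections side by side.

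**Step 1: the two sequences.**

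| Event | Text | Table 2 |
|---|---|---|
| Randomisation or allocation | Before engagement | After Engagement |
| Tailoring and staff training | After randomisation | Before Allocation |
| Consent | Staff identified during engagement, so after randomisation | Informed consent under Enrolment (whose consent is not stated) |
| T0 staff measures | After engagement, so after randomisation | T0 column, after Allocation |
| Go-live | After T0 | Same column as T0 |

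The first two rows cannot both be true. The Abstract and Study design and setting also mention randomisation before the 3-month engagement. A reserve list that is already randomised likewise suggests a list generated early. None of these sections says when a site, or the ADAPT team, learns the arm.

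**Step 2: what depends on the order.** On the text's order, staff identification, staff consent and any replacement all come after randomisation. On Table 2's order, engagement and consent come before it. T0 follows allocation on both orders, and on neither is it stated to precede disclosure. The exposure of the T0 readiness measures (ORIC, Hands4U and the study-developed items) therefore does not depend on which order is right.

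**Step 3: do the arms differ before go-live?** Mostly not. Table 1 lists the roadshow, the pre-launch poster and email, champion role definition and Portal tailoring for both arms, and training goes to all services. There are two exceptions. Interventions/groups gives Enhanced sites audit and feedback presented in person before the implementation phase, and Table 1 gives them a verbal report of the readiness data at T0, where both arms receive a written one. The newsletters, repeat posters and quarterly Portal reviews belong to the implementation period.

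**Step 4: can the blinding statement hold?** Recruitment: cancer services and staff says that the study is described in detail to prospective sites. Enhanced sites then receive monthly proactive contact and in-person presentations; Core sites receive written reports and help on request. Under Secondary outcomes, adoption is measured by staff ratings of awareness, observation and use of each strategy. A site that knows the design and is asked about each strategy can work out its arm. For staff who conduct assessments, the position is unclear rather than impossible. ADAPT research staff deliver the strategies, and ADAPT Program staff complete the strategy checklists, diaries and contact logs; whether other people conduct the assessments is not said.

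**The case against.** The strongest reply is that little harm follows even if sites are randomised first. Engagement is largely the same in both arms. The most visible differences begin after the replacement window has closed. The T0 questionnaires are completed online and downloaded automatically to limit bias. The primary outcome is extracted from the Portal, and the reserve site is itself randomised. The blinding sentence might also mean only that sites are not told the other arm's content.

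Much of this stands, and it limits the point. A reader might infer that replacement has already broken the randomisation, or that sites know their arm while replacement is still possible. The documents do not show either: concealment is asserted, and no disclosure date is given. Nor do they show that the same individuals deliver the strategies and collect baseline data.

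Three things survive. The text and Table 2 still conflict. Automatic download does not protect answers from respondents who already know their arm, and the Enhanced feedback before implementation is a difference that could reveal it. The narrow reading of blinding is not what the sentence says.

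**Conclusion.** The concern holds as an inconsistency with a conditional risk of bias, together with one statement that is wrong as written.

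- **Certain:** the text and Table 2 give incompatible orders, and sites cannot be relied on to stay blinded until completion.
- **Conditional on the text's order, and on the arm being known:** selective staff recruitment and selective site replacement.
- **Conditional only on the arm being known before T0:** a distorted baseline for hypothesis 12.

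No size can be attached, because the document gives nothing from which a bias could be calculated. The exposure is greatest for staff-reported secondary outcomes. Portal extraction limits assessor bias in the primary outcome, though not the behaviour of site staff who know their arm. A reader might go further and conclude that the arms are not comparable. Nothing in the document demonstrates an imbalance, so that conclusion is not supported. The changes are nevertheless worth making, because they are specific and cheap.

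**What to change.** 1. State one sequence, identical in the text and Table 2. The statistician may generate the list early, reserve sites included, but discloses each site's arm only once staff consent and T0 collection at that site are complete, just before go-live. Table 2 should show T0 collection, disclosure and go-live as separate steps.
2. Allow replacement only before disclosure, and report every replaced site. These are withdrawals before disclosure, not before randomisation, because the list already exists. After disclosure allow no replacement, and analyse every site in its allocated arm.
3. Replace the blinding sentence: sites and the staff who deliver the strategies are not blinded after disclosure; Portal extraction and the primary analysis use coded arms.

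The cost is protocol wording and a later release of the list by the statistician. The practical downside is timing: the Enhanced feedback before implementation and the verbal report at T0 must fit between disclosure and go-live.

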### Measures

#### Primary outcome

The primary outcome is site adherence to the ADAPT CP, operationalised as the percentage of patients at each site whose care is considered adherent to the ADAPT CP, using data extracted from the ADAPT Portal. The measure, guided by the literature on adherence [30], captures for each patient, whether they received the ADAPT CP components (screening, triage conversation, referral, referral uptake check, progress review, discharge summary, and rescreening) appropriate for their level of anxiety and depression, expressed as a continuous score of 0–100. Mean scores will be calculated for each site, averaging scores for all patients. This continuous mean score will be transformed into a binary score of adherent (≥70% of patients experiencing ≥70% of appropriate components) or non-adherent (< 70% of patients experiencing ≥70% of appropriate components), based on accepted implementation targets [31, 32].

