**Methods:**

This cluster randomised controlled trial will recruit 12 cancer service sites, stratified by size (large versus small), and randomised at site level to a standard (Core) versus supported (Enhanced) implementation strategy. After a 3-month period of site engagement, staff training and site tailoring of the ADAPT CP and Portal, each site will “Go-live”, implementing the ADAPT CP for 12 months. During the implementation phase, all eligible patients will be introduced to the ADAPT CP as routine care. Patient participants will be registered on the ADAPT Portal to complete screening for anxiety and depression. Staff will be responsible for responding to prompts to follow the ADAPT CP. The primary outcome will be adherence to the ADAPT CP. Secondary outcomes include staff attitudes to and experiences of following the ADAPT CP, using the ADAPT Portal and being exposed to ADAPT implementation strategies, collected using quantitative and qualitative methods. Data will be collected at T0 (baseline, after site engagement), T1 (6 months post Go-live) and T2 (12 months post Go-live).

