#### Primary hypothesis

Adherence to the ADAPT CP (yes/no, defined as having completed 70% or more of the recommended ADAPT CP components) will be greater in the Enhanced implementation arm than in the Core implementation arm.

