### Statistical methods

#### Sample size and justification

##### Power for primary endpoints

Based on cancer registry data for NSW (2009) (https://www.cancerinstitute.org.au/data-research/data-held-by-cinsw/nsw-cancer-registry), approximately 37,525 patients in NSW will be diagnosed with cancer in NSW each year. Based on prior epidemiological studies, 42–45% and 35–37% of these will experience mild depression or mild anxiety, respectively [3, 36, 37] and 22–36% and 20–30% will experience moderate to severe depression and/or anxiety respectively.

Based on incidence and prevalence of cancer in NSW, a conservative estimate of 464 screening events per site (total sample of 5568 screening events in 12 sites), there is at least 80% power to detect a difference in adherence rates of 30% in the Core and 60% in the Enhanced arm using a two-tailed test with Type 1 error rate of 5%. The sample size has been adjusted for the variance inflation factor due to the clustered design and can accommodate an intraclass correlation coefficient (ICC) as high as 0.14 to achieve 80% power and 0.10 to achieve 90% power [38, 39]. Although estimates of the ICC are not available, we expect the ICC will be within this range. Based on the Cancer Institute figures, we do not envisage any difficulty in recruiting the required sample for this study. Note that the number of screening events and projected sample size and power may be revised based on screening at the first three services.

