### Primary analyses

The primary analysis will be conducted using a generalized estimating equations (GEE) approach to account for the correlation of outcomes within a cluster (site) using an exchangeable covariance structure and a bias correction factor to account for the small number of clusters [39]. The dependent variable will be clinical pathway adherence and the exposure variable will be the intervention status (core versus enhanced). The unit of analysis will be at the patient level to accommodate the weighting required by unequal cluster (site) sizes. Other independent variables will be added to the model if they are independently associated with adherence and/or their inclusion in the model changes the linear coefficient of the intervention effect by more than 20% in absolute value (i.e. effect modifiers).

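### The primary outcome section ends in a site-level yes/no that cannot come from the site mean and conflicts with the patient-level yes/no that is powered and analysed

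*Protocol article*

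**What the plan says.** The Primary hypothesis uses a yes/no with a single threshold and no site rule: "Adherence to the ADAPT CP (yes/no, defined as having completed 70% or more of the recommended ADAPT CP components".

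The Primary outcome section calls the outcome site adherence and gives three site-level quantities in turn:

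- a percentage: "operationalised as the percentage of patients at each site whose care is considered adherent to the ADAPT CP";
- a mean of the 0–100 patient scores: "Mean scores will be calculated for each site, averaging scores for all patients";
- a site yes/no, said to come from that mean: "This continuous mean score will be transformed into a binary score of adherent (≥70% of patients experiencing ≥70% of appropriate components".

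Power for primary endpoints works with rates, a cluster size of 464 screening events and an ICC: "there is at least 80% power to detect a difference in adherence rates of 30% in the Core and 60% in the Enhanced arm".

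Primary analyses specifies a GEE with exchangeable correlation by site. On the unit it says: "The unit of analysis will be at the patient level to accommodate the weighting required by unequal cluster (site) sizes". On the outcome it says only: "The dependent variable will be clinical pathway adherence and the exposure variable will be the intervention status (core versus enhanced".

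Table 2 marks the primary outcome at both T1 (6 months) and T2 (12 months).

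**The concern.** Two things are wrong in the section that formally defines the primary outcome.

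First, the derivation it states cannot be carried out. A mean of patient scores does not fix the share of patients at or above 70, so the site mean cannot be turned into the 70%/70% label.

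Second, the definition ends in a label with one value per site, whereas the hypothesis, the sample size and the analysis model all fit a yes/no with one value per patient. Primary analyses does not say which form of adherence enters the model. A patient-level GEE could also take the continuous 0–100 score.

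These are different endpoints with different effect measures, and the planned power belongs to only one of them.

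**Working it through.** **1. Does the mean determine the label?** A site is adherent if at least 70% of its patients score at least 70.

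- All patients at 69: mean = 69; share at or above 70 = 0%; non-adherent.
- 70% at 70 and 30% at 0: mean = 0.70 × 70 + 0.30 × 0 = 49; share = 70%; adherent.

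The lower mean receives the better label. An adherent site has a mean of at least 0.70 × 70 = 49. A non-adherent site has a mean below 0.70 × 100 + 0.30 × 70 = 91. So only a mean below 49 or of at least 91 settles the classification.

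**2. Reproducing the plan's power.** Inputs from Power for primary endpoints: 30% vs 60%, two-sided 5%, m = 464 per site, 12 sites. Assumption: 6 sites per arm, since the article gives no allocation ratio. Design effect DE = 1 + (m − 1) × ICC; effective n per arm = 6 × 464 / DE = 2784 / DE; normal-approximation power for two proportions.

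| ICC | DE | Effective n per arm | Power | Stated |
|---|---|---|---|---|
| 0.14 | 1 + 463 × 0.14 = 65.82 | 42.3 | 80.3% | 80% |
| 0.10 | 1 + 463 × 0.10 = 47.30 | 58.9 | 91.5% | 90% |

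The stated figures are therefore those of an individual-level binary.

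**3. The same formula for a site label.** The label is constant within a site, so ICC = 1, DE = 464 and effective n = 2784 / 464 = 6 per arm. The same approximation then gives 16.8%.

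**4. Exact enumeration, 6 vs 6 labelled sites.** Two readings of the plan's rates:

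- (a) 30% and 60% are proportions of adherent sites.
- (b) 30% and 60% are patient rates, and site rates vary as Beta(p·s, (1 − p)·s) with s = 1/ICC − 1. The chance that a site rate reaches 0.70 is then 0.6% (Core) vs 28.3% (Enhanced) at ICC 0.10, and 1.9% vs 32.6% at ICC 0.14.

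Power is the sum of the binomial probabilities of all 6-vs-6 tables significant at two-sided 5%.

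| Reading | Fisher | Boschloo | Uncorrected chi-square |
|---|---|---|---|
| (b) ICC 0.10 | 0.8% | 5.6% | 21.7% |
| (b) ICC 0.14 | 1.5% | 8.5% | 27.4% |
| (a) 30% vs 60% of sites | 4.2% | 15.1% | 19.3% |

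The spread comes from the test. For 4/6 vs 0/6, Fisher gives p = 0.061 and Boschloo p = 0.021. Fisher needs at least 5/6 vs 0/6 or 6/6 vs 1/6 (p = 0.015 for each).

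**The case against.** The strongest reply is that the intended endpoint is visible. The hypothesis and the site percentage fit one measure, a patient yes/no and its site aggregate. The power calculation and the GEE fit that measure too, and Primary analyses puts the unit of analysis at patient level. Only the last two sentences of the definition, the site mean and the site label, do not fit.

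Much of this stands, and it limits the point. A reader might infer four stronger things that the article does not support:

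- **That the trial has almost no power.** No section proposes comparing 6 with 6 site labels, and the sample size is not wrong for the patient-level binary. The low power is conditional on testing the label, and its size depends on the test.
- **That the label cannot be derived at all.** It follows directly from the patient scores; only its derivation from the mean fails.
- **That a design effect cannot be applied to a site label.** It can, with ICC 1, as shown above.
- **That the two assessments in Table 2 are themselves an error.** A secondary hypothesis expects adherence to rise between 6 and 12 months, which explains them. What is unstated is which one is primary.

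The reply does not remove the contradiction. The label stands in the section that defines the primary outcome, and the analysis section names adherence without a form and so does not override it. Nor is this detail an article may leave to a fuller document: the article states a derivation that is wrong and definitions that disagree. Whether an analysis plan settles the matter cannot be seen here, so a later choice of endpoint should not be presumed.

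**Conclusion.** The definition is wrong as written and should be corrected. The site mean does not yield the site label, and the label is not the endpoint that the hypothesis, the power calculation and the GEE imply. The planned 80–90% power applies to the individual-level binary only. Were the site label the tested endpoint, power would be about 1–4% (Fisher), 6–15% (Boschloo) or 19–27% (uncorrected chi-square), far below plan under every test considered. These ranges assume 6 sites per arm and either beta-distributed site rates at the plan's own rates and ICCs, or 30% vs 60% of sites adherent. They show why the endpoint must be named; they do not forecast the planned analysis.

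**What to change.** 1. In Primary outcome, state that the primary outcome is the patient-level yes/no: at least 70% of the appropriate pathway components received.
2. In Primary analyses, name that binary as the dependent variable of the GEE.
3. State which Table 2 assessment is primary. T2, the end of implementation, is the natural choice, with the T1-to-T2 change kept as the secondary hypothesis it already is.
4. Replace the sentence that transforms the mean with one that derives the site label from the proportion of adherent patients. Deleting it outright would remove the label's only definition. Report the site mean and site label as descriptive secondary summaries.
5. Align the unit with this definition: the 5568 are screening events under Power for primary endpoints and patients under Power for secondary endpoints.

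The cost is wording only. The component data for each patient are already to be extracted from the Portal, so no new data are needed.
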